### Data and safety monitoring

2.14

The investigators will receive unified training and data monitoring committee (DMC) will be set up with experienced physicians and statisticians, who have no competing interests, to conduct monitoring once every three months for the entire research process. The trained investigators will fill out the case report form (CRF), and use EpiData 2.1a software to establish the special database system for this trial according to the items in the CRF. Two independent data administrators will type the data and conduct audits to ensure that the data in the database is consistent with the results in the CRF.

The participant will be monitored in the circumstance that an adverse event (AE) occurs, until their AE disappears. As patients diagnosed with Hyperuricemic Nephropathy frequently suffer from gout attacks, we will advise patients to oral intake anti-inflammatory drug or low-dose corticosteroids until the pain is relieved. AEs will be reported to the principal investigator to assess and the IRB. The investigator will conduct a follow-up interview and record the results supposing that the intervention induces the AE. Safety monitoring results will be reported to principal investigator weekly and the IRB.

The following are potential events related to the safety of the intervention.◆The eGFR is decreased by ≥ 50%◆The serum creatine levels is doubled than the previous blood test◆The patient is in the progression of CKD stage 5◆The patient occurs serious cardiovascular or cerebrovascular event◆The heart rate of patient is less than 40 bpm◆The patient occurs an unexpected event that is supposed to the intervention by the physicians

The following are potential SAEs.◆The patient occurs fatal or life-threatening complications◆The patient is dead or persistent and significant disabled◆The patient is hospitalized or receive large-scale medical intervention to prevent progression◆The patient develops any event that physicians diagnose to be significantly hazardous or harmful

The trial can be terminated for the following reasons.◆The number of enrolled patient is insufficient◆The allocation codes are unwrapped or the process of blinding has been nullified if the proportion of unsealed envelopes with emergency plans is more than 20% during the trial◆SAEs are supposed to associated with the intervention drug in the trial, which may signify that the safety of the drug has serious flaws

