### Blinding

2.7

This trial will be conducted in a double-blinded manner. The allocation process is blind to all individuals, including the physicians, clinical trial pharmacists, investigators, and patients, apart from the independent statisticians as they generate the random numbering.

The placebo granules and the JNSF granules will be tantamount in the matter of packaging, shape, color, and taste. The pharmaceutical company will pre-paste consecutive random numbers on the package based on the randomization schedule dispatched from the independent statistician. Patients will be given the package of JNSF or the placebo in the order of their visit by clinical trial pharmacists. The double-blind trial is divided into a primary unblinding and a secondary unblinding after the end of the last patient follow-up. The first level of unblinding is to reveal whether each patient belongs to group A or B and to facilitate comparisons between the groups by the statistician. After the statistical conclusions are obtained, a secondary unblinding is required to be informed of the medication use in each group. The independent statistician will provide the principal investigator with a set of sealed and externally numbered envelopes, which inside is the medication used. In case the serious adverse events (SAEs) occur, early broken blinding is performed by the principal investigator to estimate whether there is a connection to the intervention drug, overdose, serious drug interactions with combined drugs or the urgent need to adopt a resuscitation plan.

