### Primary outcome

2.11

The primary outcome is the eGFR value, and it is calculated using the CKD-EPI creatinine equation, to evaluate the kidney function before and after the intervention on visit 1 to 4 (listed in Table 3).

**Table 3 tbl3:** The measurement items and study procedure.

Items	Screening	Treatment			
Timepoint	V0(-1 weeks)	V1(0 week)	V2(4 weeks)	V3(12 weeks)	V4(24 weeks)
Informed consent	X				
Inclusion/exclusion criteria	X				
Demographic data	X				
Medical history	Χ				
Drug combination	Χ	Χ	Χ	Χ	Χ
Randomization		Χ			
Allocation		Χ			
Physical examination	Χ	Χ	Χ	Χ	Χ
TCM symptoms	Χ	Χ	Χ	Χ	Χ
Kidney function (eGFR, Scr, BUN, SUA)	Χ	Χ	Χ	Χ	Χ
Serum electrolytes	Χ	Χ		Χ	Χ
24-h urine test	Χ	Χ		Χ	Χ
UACR	Χ	Χ		Χ	Χ
Renal tube function	Χ	Χ		Χ	Χ
Inflammatory mediators		Χ		Χ	Χ
Renal ultrasound	Χ	Χ			Χ
Blood, urine and stool routine	Χ	Χ		Χ	Χ
Hepatic function	Χ	Χ		Χ	Χ
Electrocardiogram	Χ	Χ		Χ	Χ
Adverse events			Χ	Χ	Χ
Drug distribution		Χ	Χ	Χ	
Drug collection			Χ	Χ	Χ

X indicates that data need to be collected during the visit.

TCM, traditional Chinese medicine; eGFR, estimated glomerular filtration rate; Scr, serum creatinine; BUN, blood urea nitrogen; SUA, serum uric acid; UACR, urine microalbumin to creatinine ratio.

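### The follow-up interview after an adverse event depends on presumed causality, and for serious events causality is judged with the code open, so attribution and recorded follow-up of SAEs can be influenced by knowledge of the arm

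*Protocol article*

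**What the plan says.** Section 2.14 (Data and safety monitoring) opens its account of AEs without any causality condition: "The participant will be monitored in the circumstance that an adverse event (AE) occurs, until their AE disappears". It continues in the same way: "AEs will be reported to the principal investigator to assess and the IRB". The next sentence adds a condition: "The investigator will conduct a follow-up interview and record the results supposing that the intervention induces the AE".

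Section 2.7 (Blinding) keeps the treating and assessing staff blind: "The allocation process is blind to all individuals, including the physicians, clinical trial pharmacists, investigators, and patients". It then provides for SAEs, where "early broken blinding is performed by the principal investigator to estimate whether there is a connection to the intervention drug". Overdose, serious drug interactions and an urgent need for resuscitation are listed beside that purpose.

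Attribution is used twice more in section 2.14. One listed safety event is defined by it: "The patient occurs an unexpected event that is supposed to the intervention by the physicians". One of the reasons for which the trial can be terminated also rests on it: "SAEs are supposed to associated with the intervention drug in the trial".

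Table 3 (section 2.11) marks adverse events for collection at weeks 4, 12 and 24 for all patients; its footnote reads "X indicates that data need to be collected during the visit".

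**The concern.** Safety is a stated aim alongside efficacy, and the Background says that no clinical study has yet appraised the safety of this formulation. A fair comparison of safety between arms needs two things: the same information on each event in both arms, and causality judged without knowledge of the arm.

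The text weakens both. A site following the conditional sentence may skip the follow-up interview for an event it considers unrelated, while a site following the monitoring sentence would document that event's course. For SAEs, the judgement that decides this can be made by someone who has just seen the allocation. If a placebo allocation makes attribution to the intervention less likely, a given SAE could be followed by interview and recorded under the active granules but not under placebo. At stake are the attribution of SAEs, the completeness of their recorded course, and a termination criterion that depends on attribution.

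**Working it through.** The article gives no figure on this point: no expected AE or SAE rate, no attribution rate and no expected number of code breaks. There is nothing to reproduce or recompute, so the check sets the statements side by side.

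1. **Which steps depend on causality?**
   - Monitoring until resolution (2.14): no condition.
   - Reporting to the principal investigator and the IRB (2.14): no condition.
   - Collection at weeks 4, 12 and 24 (Table 3): no condition.
   - Follow-up interview and the record of its results (2.14): conditional on the intervention being the presumed cause.
   - Classification of an unexpected event as a listed safety event (2.14): conditional on attribution.
   - Termination of the trial because of SAEs (2.14): conditional on attribution.

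   The condition therefore reaches the interview, one event category and one termination criterion. It does not reach detection or basic reporting.

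2. **Who judges causality, and with what knowledge?** Section 2.14 sends AEs to the principal investigator for assessment. Section 2.7 has the same person open the code when an SAE occurs and gives judging the link to the drug as a purpose. Urgent resuscitation is a separate item in that list, so attribution alone is a stated reason to unblind. For non-serious AEs section 2.7 describes no early code break, and the general blinding statement applies.

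3. **Putting steps 1 and 2 together.**
   - *Non-serious AE:* attribution is blind. Conditional follow-up loses information on events called unrelated, but the rule itself does not favour an arm.
   - *SAE:* attribution can be made with the arm known. The three conditional items in step 1 can then differ by arm for the same clinical event. The SAE itself is still reported and monitored, so the count of SAEs by arm does not depend on this rule.

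4. **Could the SAE route arise in practice?** Section 2.14 counts hospitalisation among potential SAEs, and the population has CKD stages 3–4 and is treated for 24 weeks. The route is plausible, but the article gives no basis for saying how often it would be used.

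**The case against.** The strongest reply is that the conditional sentence describes an additional step for suspected drug reactions on top of universal monitoring, so the procedure is tiered and not contradictory. The English is awkward throughout, and a strict reading of one word may be unfair. Much of the safety assessment also needs no attribution: laboratory tests and electrocardiograms are scheduled for everyone, and most of the listed safety events are objective, such as an eGFR fall of at least 50%. The full protocol and the case report form (CRF) are not shown and may already hold an outcome field for every AE.

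Much of this stands. A reader might infer that AEs as such are recorded only when blamed on the intervention. The documents do not support that, given the unconditional monitoring, reporting and scheduled collection. A reader might also infer that the comparison of all AEs is biased by arm. That is not supported either, because early unblinding is described only for SAEs.

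Two further cautions are fair. Section 2.9 says the placebo contains a one-tenth portion of the drugs in the active granules, so seeing a placebo code does not by itself rule out attribution. And section 2.7 names the principal investigator as opening the code, whereas section 2.14 has an unspecified investigator conduct the interview, so the text does not say outright that the unblinded judgement governs the interview. These make the effect possible, not certain.

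What the objection does not remove is that both rules are stated. Even as a tiered procedure, the second tier is selected by attribution, and for SAEs attribution is a named purpose of opening the code. This is not detail left to a fuller document.

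**Conclusion.** The point holds in a limited form. The follow-up interview and its recorded results depend on presumed causality. For SAEs that presumption can be formed with the arm known, so SAE attribution, the recorded follow-up interview and the attribution-based termination criterion are open to influence by allocation. For non-serious AEs the consequence is lost follow-up information without directional bias. AE detection, basic reporting and the number of SAEs per arm are not affected, and the point does not concern the primary eGFR comparison.

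No magnitude can be given. Any figure would need event and attribution rates that the article does not state, and it would count follow-up records, not events. The conclusion rests on two assumptions: that the conditional sentence is applied as written, and that the principal investigator's judgement after unblinding informs the attribution used in section 2.14. It should be corrected because safety is a stated aim and the change is small.

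**What to change.** Reconcile sections 2.7 and 2.14 as follows.

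- Replace the conditional sentence with one to this effect: *the course and outcome of every AE are followed up and recorded in the CRF, whatever its presumed cause.*
- Record causality as a separate CRF item. For SAEs it is judged while the assessor is still blind. If the code has already been opened in an emergency, an investigator who has not seen it makes the judgement. Completing this item must never delay emergency unblinding.
- Remove causality assessment as a reason in itself for opening the code in section 2.7.
- Compare the arms on all AEs, with related AEs as a subset.

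The attribution that feeds the termination criterion would then be the blinded one; the criterion itself need not change for this purpose. The cost is a few sentences and a CRF instruction, somewhat more AE follow-up entries in a 118-patient trial, and the need to have an investigator available who remains blind after an emergency code break.

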### Statistical analysis

2.15

The independent statisticians will formulate a formal and detailed plan for statistical analysis prior to locking the database. Comparing the baseline demographic data of each group will use with a χ^2^ test or Student's t-test. The means ± standard deviations or medians will express continuous variables, and an independent *t*-test or the Wilcoxon rank sum test will be used to analyze differences of such variables. Repeated measures ANOVA will be built for these outcomes. The numbers and percentages will express categorical variables, and the Fisher exact test or the Mann-Whitney *U* test will be used to calculate and compare differences in such variables respectively. The missing data will be handled with multiple imputation. According to the intention-to-treat principle, all patients enrolled will be embraced in the primary analysis. An independent statistician will use SPSS 24.0 to perform the statistical analysis. Calculations will be performed using GraphPad Prism 6.01 software.

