**Methods:**

Our research is designed as a single-centre, double-blinded, randomized, placebo-controlled trial for 118 patients diagnosed with hyperuricemic nephropathy at CKD stages 3–4 and with obstruction of phlegm turbidity and blood stasis syndrome in mainland China. Patients are to be randomized into two groups: either the intervention group which receives JNSF 20.4 g/day combined with febuxostat 20–40 mg/day, or the control group which receives JNSF placebo 20.4 g/day combined with febuxostat 20–40 mg/day. The intervention will be carried on for 24 weeks. The change in estimated glomerular filtration rate (eGFR) is set as the primary outcome. Secondary outcomes include changes in serum uric acid, serum nitric oxide, urinary albumin/creatinine ratio, urinary *N*-acetyl-β-D glucosaminidase, urinary β2 microglobulin, urinary retinol binding protein and TCM syndromes in 24 weeks. Statistical analysis will be formulated by SPSS 24.0.

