#### Diagnostic criteria for hyperuricemic nephropathy

2.8.1

According to the diagnosis, syndrome differentiation, and curative effect in patients with hyperuricemic nephropathy (trial Scheme) [10], a patient must fulfill the requirements of the third item, and at least one of the five other items listed below, in order to be diagnosed with hyperuricemic nephropathy.(1)The patient should be a middle-aged male or post-menopausal female who has often had gouty arthritis, gout nodulosis, or uric acid stones in the urinary trac.(2)The patient should demonstrate clinical manifestations of chronic interstitial glomerulonephritis, including mild to moderate proteinuria or decreased urinary concentrations (low osmotic pressure in the first-morning urine) in the early stage, and hypertension and azotemia in the later period.(3)Serum uric acid levels should be > 357 μmol/L for females and >417 μmol/L for males.(4)Urine sediment examination results should demonstrate uric acid crystallization, microscopic or gross hematuria, and pyuria.(5)Urine sediment examination results should demonstrate uric acid crystallization, microscopic or gross hematuria, and pyuria.(6)Renal histology is mainly manifested as renal tubule-interstitial lesions, and birefringent needle-like urate crystals are found in the renal interstitium and renal tubules.

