### Secondary outcomes

2.12

1Biological indicators: Serum creatinine (Scr), serum uric acid (SUA), blood urea nitrogen (BUN), serum nitric oxide (NO), xanthine oxidase (XOD), 24 h proteinuria, 24 h urine uric acid, urine microalbumin to creatinine ratio (ACR), urinary β2 microglobulin (β2-MG), urinary *N*-acetyl-β-D glucosaminidase (NAG), and urinary retinol-binding protein (RBP) levels will be tested in the clinical laboratory.2Inflammatory mediators: Blood plasma levels of interleukin 1β (IL-1β), interleukin 18 (IL-18), and monocyte chemoattractant protein 1 (MCP-1) will be measured as they are indicative of systemic inflammation, whereas the protein and mRNA expression levels of NLRP3 and Caspase-1 will be measured to assess the inflammatory characteristics of peripheral blood mononuclear cells (PBMCs). Plasma and serum samples will be stored at - 80 °C.3The scores for the curative effect associated with TCM syndromes.

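### Serum uric acid and 24 h urine uric acid are to be compared without their week-0 value as covariate; adjusting for it is usually more precise and needs no new data

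*Protocol article*

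**What the plan says.** Section 2.15 of the protocol article gives the method for continuous variables: "an independent *t*-test or the Wilcoxon rank sum test will be used to analyze differences of such variables". It then adds: "Repeated measures ANOVA will be built for these outcomes". Neither of the two-group tests takes a covariate, and none is named for the ANOVA. The same section announces a later document: "The independent statisticians will formulate a formal and detailed plan for statistical analysis prior to locking the database".

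Section 2.12 lists both measures among the secondary outcomes: SUA, and "24 h proteinuria, 24 h urine uric acid". The abstract describes SUA as a change: "Secondary outcomes include changes in serum uric acid".

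Table 3 (section 2.11) schedules the row "Kidney function (eGFR, Scr, BUN, SUA") at screening, week 0 (V1), week 4 (V2), week 12 (V3) and week 24 (V4). The row "24-h urine test" is scheduled at screening, week 0, week 12 and week 24. I read that row as including urine uric acid.

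**The concern.** A baseline value of each outcome will be collected, but the stated analysis does not use it efficiently. A t-test on week-24 levels ignores it. A t-test on change from baseline uses it but fixes its slope at 1 instead of estimating it. With two time points, the group-by-time test of a repeated measures ANOVA is that same change-score test, so the ANOVA does not by itself cure the problem.

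What is at stake is precision in two secondary comparisons. Section 2.5 sizes the trial on eGFR alone, so neither urate outcome has its own power calculation. Both arms receive febuxostat (section 2.9), and the Discussion concedes that the herbal formulation may lower uric acid less than febuxostat does. Any added urate effect may therefore be modest. No claim is made here about eGFR or the sample size.

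**Working it through.** **The plan's own figure.** The article gives no calculation for the urate outcomes, only one for eGFR: difference 10, SD 18.1, 5% type I error, 80% power. The normal approximation, two-sided, gives 2 × (18.1 × 2.802 / 10)² = 51.4, or 52 per group. The t-distribution version gives 52.4, or 53, as stated. Then 53 / 0.9 = 58.9, or 59 per group and 118 in total. The figure reproduces, and 53 per arm is used below only as a realistic group size.

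**Inputs not in the article (assumptions).** r is the correlation between the week-0 and week-24 values. k is the week-0 SD divided by the week-24 SD. I take r = 0.3, 0.5, 0.7 and k from 0.7 to 1.2. A k below 1 is plausible for SUA because entry requires a value above a threshold (section 2.8.1: "a patient must fulfill the requirements of the third item"), which narrows the baseline distribution.

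**Variance of the treatment comparison**, in units of the week-24 variance:
- t-test on week-24 level: 1
- t-test on change: 1 + k² − 2rk
- ANCOVA on the week-0 value: 1 − r²

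**ANCOVA relative to each t-test:**

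| Comparator | r = 0.3 | r = 0.5 | r = 0.7 |
|---|---|---|---|
| Week-24 level, any k | 0.91 | 0.75 | 0.51 |
| Change, k = 1.2 | 0.53 | 0.60 | 0.67 |
| Change, k = 1 | 0.65 | 0.75 | 0.85 |
| Change, k = 0.85 | 0.75 | 0.86 | 0.96 |
| Change, k = 0.7 | 0.85 | 0.95 | 1.00 |

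Worked example, k = 1, r = 0.5: (1 − 0.25) / (1 + 1 − 1) = 0.75. When k = r the ratio against change is exactly 1, as in the bottom right cell.

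**Cost of the covariate.** The variance is multiplied by about 1 + 1/(N − 4): 1.009 at N = 118 and 1.010 at N = 106. The worst cell is therefore a loss of about 1%.

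**In patients.** With equal SDs, 53 per arm act like 53/0.65 = 82, 53/0.75 = 71 and 53/0.85 = 62 per arm against the change-score test, before that 1%.

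**Detectable difference** at 53 per arm, 80% power and k = 1, in SD units: 2.802 × √(2v/53), where v is the variance above. Level: 0.544 at every r. Change: 0.644, 0.544, 0.422. ANCOVA: 0.519, 0.471, 0.389 (r = 0.3, 0.5, 0.7).

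**Simulated power** (53 per arm, effect 0.5 week-24 SD, 4,000 runs):

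| k, r | Change t | Level t | ANCOVA |
|---|---|---|---|
| 1, 0.3 | 58% | 73% | 77% |
| 1, 0.5 | 71% | 72% | 83% |
| 1, 0.7 | 91% | 72% | 95% |
| 0.7, 0.5 | 81% | 73% | 83% |
| 0.7, 0.7 | 95% | 72% | 95% |

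Null rejection was 4.2–5.2% throughout, so all three tests are valid.

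**Against the repeated measures ANOVA** (group-by-time, Greenhouse–Geisser, SUA at four visits, equal correlation between visits), power for the ANOVA and then for week-24 ANCOVA:
- k = 1, r = 0.5: 74% and 83% with a constant effect from week 4; 60% and 83% with an effect growing 0.17, 0.33, 0.5
- k = 0.7, r = 0.7: 97% and 95% (constant); 88% and 95% (growing)
- three visits, as for the 24-h urine, k = 1, r = 0.5, constant effect: 75% and 84%

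**Same estimand on both sides.** Take the mean of the three post-baseline SUA visits, k = 1, r = 0.5, constant effect 0.5. The variance of that mean is (1 + 2 × 0.5)/3 = 0.667. Its change from baseline has variance 0.667 + 1 − 2 × 0.5 = 0.667; with ANCOVA it is 0.667 − 0.25 = 0.417, a ratio of 0.625. The corresponding power is about 88% without and 97% with the covariate.

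**The case against.** The strongest objection is that covariates for secondary outcomes belong in the detailed plan that section 2.15 announces, and that naming no covariate in a condensed article does not exclude one. It is true that the later plan could add one. But the section already names the tests, and the t-test and the rank sum test cannot take a covariate. The point is about that stated choice, and the announced plan is the natural place to change it.

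Second, the repeated measures ANOVA normally takes week 0 as a response level, so baseline is not wholly ignored. In addition, the omnibus group-by-time test spends three degrees of freedom, so part of its shortfall against week-24 ANCOVA is not due to baseline adjustment. Both points stand. A one-degree-of-freedom contrast from the same ANOVA does better than the omnibus test. At k = 1, r = 0.5, the post-baseline mean minus week 0 reaches 88% with a constant effect, above the 83% of week-24 ANCOVA. With a growing effect, a linear-trend contrast reaches 77%, against 83%. Week-24 ANCOVA is therefore not best in every setting. On the same estimand, however, the adjusted test still gains: 97% against 88%.

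Third, r and k are unknown. Titrating febuxostat to target may lower r for SUA; at r = 0.2 the gain over a level test is only 1 − 0.96 = 4%. This stands as a limit on size. A low r, however, enlarges the gain over the change score when the SDs are equal. The rank sum option was not evaluated.

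Finally, these are secondary outcomes and the planned tests are valid. That is correct, and it is why the point is rated as a desirable improvement only.

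**Conclusion.** The point holds as one of efficiency. The stated analysis is unbiased and controls type I error, but it leaves precision unused. With equal SDs and r between 0.3 and 0.7, adjustment cuts the variance by 35% to 15% against a change-score t-test, and by 9% to 49% against a week-24 level t-test. If baseline spread is much smaller than week-24 spread (k = 0.7), the result against the change score runs from a 15% reduction to a loss of about 1%. All these sizes rest on assumed r and k, and on reading the 24-h urine row of Table 3 as covering urine uric acid. The sponsor cannot know r and k in advance, and so cannot know whether the level or the change test would serve better. ANCOVA at week 24 is at least as precise as either, to within about 1%.

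**What to change.** In section 2.15, or in the detailed plan before database lock, state that SUA and 24 h urine uric acid at week 24 will be compared by ANCOVA, or by a repeated-measures model of the post-baseline visits, with the week-0 value of the same outcome as covariate. Keep the unadjusted test as a supporting result. Prior urate-lowering therapy is at most an optional sensitivity covariate, if it can be coded from the screening medication or history records; no benefit is claimed for it.

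The change is one of analysis wording. The week-0 values are already scheduled, so it needs no extra visit, test or patient. The statistical cost is one degree of freedom, about 1% of variance.

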### Sample size

2.5

The sample size is issued from the primary outcome that is an alteration in baseline estimated glomerular filtration rate (eGFR). According to a previous report [8], the average eGFR value of the control group is estimated to be 34.7 mL/min/1.73 m^2^. After treatment with JNSF, the value for the intervention group could be increased by 10 mL/min/1.73 m^2^, and its standard deviation would be approximately 18.1 mL/min/1.73 m^2^. If we set the type 1 risk level at 5% and the power at 80%, we calculated that the minimum sample size for each group is 53 participants, using the formula: $t=\frac{\bar{x_{1}}-\bar{x_{2}}}{\sqrt{\frac{\left(n_{1}-1\right)s_{1}^{2}+\left(n_{2}-1\right)s_{2}^{2}}{n_{1}+n_{2}-2}\left(\frac{1}{n_{1}}+\frac{1}{n_{2}}\right)}}$. Assuming a drop-out rate of approximately 10%, we determined that the sample size should be increased to 59 in both groups, to include a total of 118 patients.

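### The primary eGFR outcome is worded as a change in some places and as the value over visits 1 to 4 in another, and no single baseline-adjusted week-24 comparison is fixed

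*Protocol article*

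**What the plan says.** The primary outcome is described in three places.

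- Abstract, Methods: "The change in estimated glomerular filtration rate (eGFR) is set as the primary outcome". The sentence gives no time point; week 24 is implied by the length of treatment.
- Section 2.5, Sample size: "the primary outcome that is an alteration in baseline estimated glomerular filtration rate (eGFR", again a change. The sizing inputs that follow are worded as group levels: "the average eGFR value of the control group is estimated to be 34.7 mL/min/1.73 m^2", and "the value for the intervention group could be increased by 10 mL/min/1.73 m^2", with a standard deviation (SD) of 18.1.
- Section 2.11, Primary outcome: the eGFR value, used "to evaluate the kidney function before and after the intervention on visit 1 to 4". Table 3 places these visits at weeks 0, 4, 12 and 24.

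Section 2.15, Statistical analysis, gives general rules for continuous variables: "an independent *t*-test or the Wilcoxon rank sum test will be used to analyze differences of such variables", and then "Repeated measures ANOVA will be built for these outcomes". It names no ANOVA term, deciding visit or baseline covariate. It plans multiple imputation and an intention-to-treat primary analysis, and it announces a detailed analysis plan before database lock.

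**The concern.** A change to week 24 and a set of values over four visits, one of them before treatment, are different endpoints, so the text leaves two candidates for the primary outcome. The methods in Section 2.15 do not settle the choice, because each reading of them tests something different:

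- A t-test or Wilcoxon test at week 24 compares groups at one time, on the value or on the change.
- The ANOVA group main effect compares averages over all included visits. If week 0 is included, it dilutes the treatment effect.
- The ANOVA group-by-time term asks whether the two profiles differ in shape anywhere. With four visits it has 3 degrees of freedom and is not the week-24 contrast.

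At stake are a clear answer to the trial's main question and the power of the test taken as decisive. In addition, eGFR is measured at baseline in every patient, yet no test is planned with it as a covariate.

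**Working it through.** **Inputs from Section 2.5:** difference 10, SD 18.1, type 1 risk 5%, power 80%, 53 per arm, 59 per arm after 10% drop-out. **Assumed, not in the documents:** equal correlation r between visits, from 0.5 to 0.9; an effect growing linearly with time; 18.1 as the SD of the eGFR value (the alternative is in step 6).

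**1. The plan's own figure.** n per arm = 2 × (1.96 + 0.84)² × (18.1/10)² = 51.4, so 52. With the t distribution it is 52.4, so 53. Power at 53 per arm is 80.4% (81.2% by the normal approximation). 53/0.9 = 58.9, so 59 per arm and 118 in total. The size reproduces as an unadjusted two-sided two-sample t-test.

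**2. ANOVA group main effect over visits 1 to 4.** A linear effect of 10 at week 24 gives 0, 1.67, 5 and 10 at weeks 0, 4, 12 and 24. The average is 16.67/4 = 4.17. The SD of a patient's four-visit mean is 18.1 × √((1 + 3r)/4), and the standard error is that SD × √(2/53).

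- r = 0.5: SD 14.31, SE 2.78, ratio 4.17/2.78 = 1.50, power 32%.
- r = 0.9: SD 17.41, SE 3.38, ratio 1.23, power 23%.

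The time course matters. With the full effect from week 4 the average is 30/4 = 7.5. The ratios are then 7.5/2.78 = 2.70 and 7.5/3.38 = 2.22, and power is about 77% and 60% (normal approximation). The average is still not the week-24 effect of 10.

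**3. Change-score t-test.** SD of the change = 18.1 × √(2(1 − r)): 18.1 at r = 0.5, 14.02 at 0.7, 11.45 at 0.8.

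**4. ANCOVA at week 24.** Residual SD = 18.1 × √(1 − r²): 15.68 at r = 0.5, 12.93 at 0.7, 10.86 at 0.8.

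**5. Power at 53 per arm, 10-unit effect at week 24 (t or F distribution).**

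| r | Group main effect | Group-by-time (3 df) | Week-24 value t-test | Change t-test | ANCOVA |
|---|---|---|---|---|---|
| 0.5 | 32% | 73% | 80% | 80% | 90% |
| 0.7 | 27% | 93% | 80% | 95% | 98% |
| 0.8 | 25% | 99% | 80% | 99% | >99% |
| 0.9 | 23% | >99% | 80% | >99% | >99% |

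Simulation with 3,000 runs at r = 0.5, 0.7 and 0.8 agrees within about 2 points (main effect 31%, 25%, 23%; ANCOVA 90%, 98%, >99%).

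**6. If 18.1 is the SD of the change.** The change t-test then has 80% power whatever r is. The SD of the value is 18.1/√(2(1 − r)), so the ANCOVA residual SD is 18.1 × √((1 + r)/2): 15.68, 16.69 and 17.17 at r = 0.5, 0.7 and 0.8. ANCOVA power is 90%, 86% and 84%.

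**The case against.** The strongest reply is that Section 2.15 gives general rules, labels no test as the primary eGFR analysis, and defers detail to a later analysis plan that may name the contrast and the covariate. This stands as far as missing detail goes. It does not remove the conflict between Section 2.11 and the Abstract and Section 2.5, which that plan would first have to resolve. Nor does it make the listed tests interchangeable.

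Some stronger readings are tempting, but the documents do not support them:

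- *Baseline is ignored.* A change score and a group-by-time term both use the baseline value. The accurate statement is that no baseline covariate is named.
- *The trial is underpowered.* The stated size reproduces, and the unadjusted t-test keeps its planned 80% at 10 units. The loss is relative to ANCOVA. Setting the main effect against ANCOVA alone would mislead, because the change t-test and the interaction come close to ANCOVA at high correlation.
- *The type I error is inflated.* If success were claimed on any of the change t-test, ANOVA main effect and interaction, simulation under no effect gives about 13%. The protocol does not say that success would be claimed in this way.
- *The tests cannot be combined with multiple imputation.* Imputation removes the loss of incomplete cases. The two-group main effect is a single contrast that pools directly, and pooling methods exist for the interaction.
- *The later plan cannot cure this.* Nothing in Section 2.15 prevents it from naming one contrast and adding baseline eGFR.

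**Conclusion.** The point holds as an inconsistency in the primary outcome combined with an unranked set of tests, one reading of which does not estimate the week-24 change. That the main effect is diluted follows from randomisation, since the expected week-0 difference is zero; it needs no assumed correlation. The size does depend on assumptions: about 23 to 32% power for a linear build-up to 10 units and correlations of 0.5 to 0.9, and more if the effect appears early.

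A valid analysis with about 80% power or more is already within the plan's wording. Baseline adjustment improves on it by about 10 points at correlation 0.5. At 0.7 the gain is about 17 points over the value t-test and 2 over the change t-test. At 0.8 or above it is negligible against the change t-test, unless 18.1 is the SD of the change, in which case it is about 4 points at 0.8. This is a change that should be made because it is nearly free. It is not a defect that invalidates the design.

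**What to change.** Use one definition in the Abstract and Sections 2.5, 2.11 and 2.15: the primary comparison is the difference between JNSF and control in eGFR change from baseline to week 24. Test it two-sided at 5%, by either of these:

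- ANCOVA at week 24 on the multiply imputed data, with baseline eGFR as covariate; or
- a mixed model on visits 2 to 4 with treatment, visit, treatment-by-visit and baseline eGFR, taking the week-24 contrast.

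Name which of the two is primary, and say which measurement is the baseline, since Table 3 schedules eGFR at both screening and week 0. With baseline as covariate, ANCOVA gives the same treatment estimate for the week-24 value and for the change, so the value-or-change question no longer affects the test. State in Section 2.5 whether 18.1 is the SD of the value or of the change. Label the unadjusted t-test, the Wilcoxon test and the repeated measures ANOVA as supportive.

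The cost is wording in the protocol and the analysis plan. All visits are already scheduled, no new data are needed, and SPSS fits both models.
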